**Figure 2. f2:**
[figure not shown]
MindKind app study design. The 12-week study is composed of three, four-week rotations focusing on four active ingredients influencing mental health (sleep, body movement, social connections and positive experiences). Participants will be randomized into one of two arms: the first of which allows participants to select their AIs of focus and the second of which randomly assigns the AIs to which participants are exposed. In this example, the ARM 1 participant has selected the topics Body movement, Positive activities and Social connections for their topics, while the ARM 2 participant has been randomly assigned to Sleep, Positive activities and Body movement for their 3 AI topics.

In order to understand whether the choice of survey domain impacts a participant’s short- or long-term engagement in the study, we will independently randomize participants into two different arms (in equal proportion). Participants in the first arm select their AI topic at the beginning of weeks one, five, and nine. Participants in the second arm are randomly assigned to their AIs for each of the three, four-week rotations (
Figure 2).

*Recruitment*

The quantitative substudy aims to recruit 4500 young people (1500 from each country) to download the study app, with a minimum of 10% of the 4500 young people recruited having lived experience of anxiety and depression. The sample size was selected based on expected engagement
^
13
^ in order to achieve a program goal of 100 participants per country completing the 12-week study.

Rolling recruitment will begin in the third quarter of 2021. Youth will be recruited in the following ways:

1.Through social media given limitations on in-person activities during the ongoing COVID-19 pandemic. Posts and advertisements will be placed on popular youth accessible social media platforms such as Instagram, Twitter, Facebook, LinkedIn, Reddit, and WhatsApp to reach young people in each of the three study countries.2.To ensure that data collection is representative of a broad population in each country, the three sites will collaborate with intersectoral organisations (organisations working on sexual and reproductive health research, disabilities, sexuality, race/caste etc) with the help of emailers and posts.3.Each of the sites will also reach out to partner (youth) organisations and spread the word within their networks along with using existing researcher contacts.4.We will also recruit students at educational institutions (e.g., schools, colleges and universities) with the help of posters/flyers, and existing contacts between the site team and identified institutions.5.Networks of young people will be tapped into by PYA and YPAG participants for snowball recruitment.

Recruitment materials such as social media posts, posters, flyers, videos etc, will be developed in English for all the three sites. Additionally, to reach a more diverse population, recruitment materials will be translated to other languages in South Africa (IsiXhosa and seSotho) and in India (Hindi, Marathi and Tamil). However, the study app will be available only in English.

Youth co-researchers have been heavily involved in the development of recruitment plans, providing feedback on the recruitment materials and helping disseminate the final materials to ensure that all recruitment materials are youth friendly and culturally appropriate.

Due to concerns about cellular data costs in South Africa, study participants in this country will be given a small stipend to subsidize their data plans in order to facilitate participation. Stipends of R150 will be paid per four weeks of participation in the quantitative substudy. Similarly, a small stipend pool exists for participants in India who find it difficult to pay for data. However, given the relatively low expense for cellular data in India , the need is not expected to be widespread. No stipends are offered for participants of the quantitative substudy in the UK.

*Data collection*

On enrolment, a baseline survey is administered to catalogue the participant’s background and experiences with mental health. For ease of administration, these are divided into four sections. ‘About you’ includes the topics demographics and socio-economic status (Appendix 3
^
23
^,
*Extended data*). ‘Your environment’ includes food security (USDA Food insecurity survey (six-item))
^
24
^, neighbourhood safety and cohesion questions (PhenX Neighbourhood Safety, and PhenX Collective Efficacy)
^
25
^ and questions related to history of exposure to violence (Appendix 3
^
23
^,
*Extended data*). ‘Your habits’ includes questions pertaining to hobbies, physical activity and phone use habits (Appendix 3
^
23
^,
*Extended data*). ‘Your health’ includes questions pertaining to physical ability (WHODAS 2.0 (12-item)
^
26
^), depression (PHQ-9
^
27
^), anxiety (GAD-7
^
28
^), and history and management of mental health (Appendix 3
^
23
^,
*Extended data*). These baseline questionnaires are administered on study day zero (
Figure 3). On the following day, participants begin their first AI-rotation for weeks one to four. The second and third rotations occur weeks five to eight and nine to 12, respectively (
Figure 2).

**Figure 3. f3:**
[figure not shown]
Baseline, daily, and weekly surveys. MindKind is a 12-week study consisting of a baseline survey followed by four-week rotations focusing on a single “active ingredient” (AI). On the seventh day of the week, a long survey is administered consisting of a standard instrument pertaining to the topic of the AI, as well as PHQ-9 and GAD-7. Preliminary testing showed that this weekly survey took 9 minutes on average (range 3 to 22 min). During the remaining days participants receive short questionnaires including a standard mood question and three to five AI-specific questions. Preliminary testing indicated that the daily surveys took no more than 5 minutes to complete (range 30 sec to 5 min). Participants are prompted to journal on one of those days. At the beginning of weeks five and nine, a new AI is presented (Arm 2) or selected by the participant (Arm 1). This design was selected based on feedback from the PYAs and YPAGs to minimize burden to participants while still collecting rich longitudinal data. PYAs and YPAGs were also consulted in the selection of the specific AIs chosen for implementation.

**Surveys and active data collection:** The questions posed to participants throughout the study focus on the interplay between mood and four different AIs (sleep, social connections, body movement or physical activity, and positive activities) (
Figure 2–
Figure 3). Study participants focus on one AI at a time, in four-week rotations. On days one to six of the week, participants are asked a standard mood question:

Pick the response that describes how you felt today:

○Worst ever○Bad mood○Average○Good mood○Best ever

along with a short (three to five item) AI-specific questionnaire (Appendix 2
^
29
^,
*Extended data*). They are also prompted to journal on an AI-specific or general topic on one of those days. On the seventh day, participants are asked to complete a long survey related to their AI topic (Insomnia Severity Index (seven-item)
^
30
^, UCLA Loneliness Scale (three-item)
^
31
^, International Physical Activity Questionnaire (seven-item)
^
32,
33
^, Behavioural Activation for Depression Scale
^
34
^ for the sleep, social connections, body movement and positive activities AIs, respectively), as well as PHQ-9
^
27
^ and GAD-7
^
28
^ to get a deeper understanding of their mood (
Figure 3).

**Passive data collection:** Participants can opt in to provide passive data collection about their phone activity and environment in order to understand their phone use habits. The statistics collected are daily screen time (a daily log of when the phone’s screen is unlocked), charging time (a log of when the phone is connected to its charger), battery statistics (a log of battery charge throughout the day via the Android ACTION_BATTERY_CHANGED call), data usage (hourly reporting of amount of data transmitted and received), ambient light as measured by the phone’s light sensor (sampled for ten seconds every five minutes in order to minimize battery consumption). No information will be collected that could violate a participant’s privacy, such as information about specific activities or apps used on the phone, call logs, or the content of messages. No identifiable location data will be collected.

**Technical implementation:** The study will be implemented in two separate pieces of technology. Eligibility checking, account creation and enrolment occurs via a website which has been optimized for mobile device experiences. Once a participant has enrolled, they are prompted to download the MindKind Study App from the Google Play store. The app requires an Android phone running Android 5.0 or higher. Participants use their phone number as a mechanism to create an account on the enrolment website, and to login to their account on the study app. Each time they request to login, a unique code sent to their phone via SMS validates their login. Due to SMS messaging restrictions, participants located in India created a 6-digit PIN in lieu of SMS validation for login.

Both applications will store data in the Bridge Server, a set of web services developed and operated by Sage Bionetworks. Bridge exposes a REST style web services API designed to allow collection and management of mobile health data from a variety of apps. This service has been used by Sage and other research organizations to support a variety of health studies on both the Android and iOS platforms. Bridge provides apps the ability to securely create accounts for participants, and record consent and other personal information separately from study data intended to be shared with research teams.

**Data management:** Data from both the enrolment website and study app will be sent to Sage Bionetworks’ Bridge Server as json files. Coded study data, consisting of survey responses and passive data measurements, will be exported to Sage’s data sharing service, Synapse, for access by the study team
^
35
^. Synapse is a general-purpose data and analysis sharing service where members can work collaboratively, analyse data, share insights and have attributions and provenance of those insights to share with others. Synapse is developed and operated by Sage Bionetworks as a service to the health research community. Programmatic access to Synapse via R and Python Clients allows us to curate the json files from the surveys into tabular formats by survey type in order to allow for analysis.

**Data protection:** The data collected through the phone app will be encrypted on the participant’s phone. The app will not access other applications or user contacts, photos, texts, or emails on the participant’s phone. Identifiable account information will be stored separately from participants’ study data, and the encrypted mapping between personally identifiable information and the de-identified study data is only accessible by key personnel with controlled access. The de-identified coded study data will be stored on Synapse as described above.

We maintain strict information technology procedures to safeguard information and prevent improper access. Our Information Security Program is based on the ISO 27000 series of Information Security Management System standards and is supported by special NIST publications. The Bridge server and Synapse research environment run on Amazon Web Services (AWS) S3 Cloud-based infrastructure. It is protected by data privacy and security controls standards in healthcare information technology, including the provisions required by HIPAA/HITECH and GDPR. Files and database storage supporting the application are encrypted with AES-256. Transmissions through Synapse interfaces are encrypted with SSL/TLS, enforced by technical policy. Synapse operates under an IRB-approved governance process that includes well-documented Terms and Conditions of Use, guidelines and operating procedures for handling data, data security measures with strict information and privacy-enhancing technologies, as well as the right of audit and external reviews. These end-to-end security and end-to-end privacy measures safeguard the confidentiality and integrity of the data.

*Data analysis plan*

All analyses described below will be performed within-site as well as across-site, adjusting for site. A sensitivity analysis will be performed, excluding South Africa, due to the potential confounding introduced by participant payment.

**Governance preference:** This analysis leverages the Group A (
Figure 1) selections for Option 1 and Option 2 to understand the degree to which study participants have a preference about how their data are accessed, both on who determines which investigators can access the data, and by what means they access the data. Outcome variables for this aspect of the substudy are the prospective participant’s (1) model choice for governing standard for the data and (2) model choice for researcher access to the data. The primary analysis will be a summarization of participant preference for each of the two questions. A chi-square test will be used to assess the statistical significance of the differences observed between the three options. A secondary set of analyses will assess the degree to which age, gender, and self-reported present or past mental health issues are associated with governance model preference, both globally and within-site. This analysis will also be performed with a multinomial logistic regression adjusting for these three variables.

**Governance acceptability:** This analysis leverages the enrolment rate for Groups B-D to understand the degree to which a governance model that improves usability and access by investigators, affects study enrolment over models that give participants more control (i.e. democratic determination of data terms) and offer better data security (i.e. secure server access only). The outcome variable for this aspect of the substudy is whether or not the prospective participant enrolled (yes/no). A logistic regression to test the effect of the governance model will be fit, adjusting for age, gender, self-reported present or past mental health issues, and site (global model only). The primary comparisons of interest are Group C vs Group B (democracy vs current norms) and Group D vs Group C (server access vs data download). A secondary analysis will test an interaction term between the model and self-reported mental health issues.

**Engagement:** The goal of this portion of the study is to understand participant engagement and compliance with the study protocol during the course of the 12-week study. We will measure participant engagement based on the following metrics: 1) study completion rates, i.e. proportion of participants that remain active in the study through 12 weeks as well as interim time points (e.g. four and eight weeks); 2) types of data (surveys and passive data streams) shared by participants and for how long; 3) total active tasks completed; 4) time to dropout (i.e. time point of the last task completed).

For study completion and interim participation, the binary outcome variables ‘participation at time X’ (yes/no) can be modelled using logistic regression to test the effect of the engagement model, adjusting for various socio-demographic factors (e.g. age, gender, self-reported history of mental health challenges), governance model (self-choice, or specific model presented) and site (global model only). For total task completion, the number of tasks completed by a participant will be modelled using Poisson Regression using the same independent variables as previously stated. For assessing the types of data shared by participants, we will compute the aggregate statistics on the number of unique data types shared by participants and for how long. Using a logistic regression model, we will assess the potential differences in data sharing aggregate statistics. Time to dropout can be analysed using a proportional hazards model with censoring at the study end. For each of these three analyses, we will also secondarily examine the effect of the governance model on engagement.

**
*Qualitative substudy*
**

*Study design*

The qualitative substudy aims to (1) identify the consensus data governance model(s) for an open yet privacy-preserving global mental health databank, from the perspective of multinational young people; and (2) understand the concerns, hopes, and expectations of multinational youth for such a databank with regards to the return of value to youth participants and youth participation in databank governance (
Table 2). We will employ a deliberative democracy approach for this study
^
18
^. Deliberative democracy is a method for community engagement in the complex ethical issues surrounding emerging technologies for which most people have not yet formed strong opinions. Deliberative democracy is a distinct qualitative research approach, differing from focus groups by the purposeful provision of educational intervention to enrich group discussion. Further, there is an emphasis on discussion leading to iterative revision of opinions as participants integrate new information and others’ perspectives.

We will conduct two rounds of deliberative democracy sessions. In the first round, up to ten cohorts of five to seven participants will be convened per country (approximately 150 total participants). A sample size of n=50 per site is characteristic of deliberative democracy studies
^
36
^. The individual group size of five to seven participants is characteristic of a typical small group in in-person studies
^
36,
37
^. Each will explore data governance models and voice their concerns and hopes regarding data governance for a global mental health databank for youth, identifying points of consensus and disagreement. Standard educational materials will be co-created and disseminated prior to the deliberative sessions to prepare participants. These materials may be disseminated as written or in other multi-media formats (e.g., audio, video). Participants will have the opportunity to ask the research team any questions prior to the sessions. Cohorts will meet virtually for up to two hours.

In the second round of deliberation, we will convene up to ten multinational cohorts; all participants in the multinational sessions will be drawn from the first round. Again, cohorts will meet for up to two hours in two 60-minute sessions. Each cohort includes six to eight participants: two to three participants from each country (60 total participants).

This arrangement of sessions allows participants to: 1) develop expertise over time both with content and with the deliberative approach; 2) appreciate the similarities and differences between country-specific and multinational perspectives on data governance; 3) reflect on the intersection of these topics with their own lived experience.

The quality of deliberative democracy sessions will be evaluated using criteria proposed by DeVries
*et al.*, 2010
^
37
^, including equal participation of all participants, respect for the opinions of others, willingness to adopt a social (rather than individualistic) perspective, and reasoned justification for one’s positions. These data will be gathered by the research team participant exit surveys.

*Co-creation*

YPAGs and the IYP engaged in co-design with the academic study team on the following topics: a) ensuring representation from marginalized and vulnerable groups in recruitment and participation; b) developing study materials including: informed consent, educational materials, and facilitator guides; c) identifying the challenges of virtual discussions and developing mitigation strategies to address equal engagement and power imbalances; d) planning for involving youth co-researchers in data analysis; e) dissemination of and access to study findings in a way that is engaging and inclusive of the people who have participated.

*Recruitment*

Participants will be recruited directly through YPAG members and existing volunteer rosters, existing researcher contacts, and snowball recruitment through these contacts. Further, social media (passive, active), direct email advertising, and posters may be used. Additionally, a single-time pop-up message in the MindKind app will recruit from young people participating in the quantitative substudy with a goal that half have previous exposure to the study. Young people with lived experience of anxiety and/or depression will be preferentially enrolled.

Deliberative sessions will be stratified by age and co-enrolment or lack of co-enrolment in the quantitative substudy. Youth will participate in sessions with others of similar age. For single country sessions, there will be up to three age cohorts (e.g., 16- to 17-year-olds in the UK; 18- to 20-year-olds in all countries; 21–24-year-olds in all countries). For multinational sessions, there will be at least two age cohorts (e.g., 16- to 20-year- olds; 21- to 24-year-olds). In single country sessions, we will aim for an equal distribution of participants across these two variables (i.e., age and co-enrolment in the quantitative substudy), but will have no fewer than one-third in each category, except for the UK age groups, which will have no fewer than one quarter of the total UK study population enrolled in any one age category. Additionally, we will seek a sample from a diversity of backgrounds in relation to gender, geographic location, socioeconomic status, educational attainment, ethnicity, religion, and first language. We will continue sampling participants until we have recruited a diverse set of individuals.

Given the amount of time required for pre-learning activities and participation, qualitative substudy participants will receive a modest incentive for participation in the form of a gift card (UK, India) or airtime voucher (South Africa).

*Data collection and analysis*

There are two primary outputs of deliberative democracy processes: deliberative output and analytical output
^
38
^. Deliberative outputs are statements of consensus or disagreement that arise directly from discussants. These statements will be captured by the facilitator and will be ratified by discussants themselves before the end of their cohort session. We will employ the framework method
^
39
^ to capture analytical outputs regarding concerns, hopes, and expectations of discussants on return of value for participation in such a databank and the concerns, hopes, and expectations of discussants regarding youth participation. The framework approach is particularly useful in multi-disciplinary research teams that include lay people with less qualitative data analysis experience.

Discussion session data will be transcribed verbatim, de-identified, and checked for quality against audio recordings by the academic research team. De-identified transcripts will be uploaded to a cloud-based qualitative data analysis platform (NVivo). The academic research team, in collaboration with youth researchers, will code each transcript on this shared platform. The study team will identify
*a priori* codes based on study goals, and emergent codes will be developed iteratively during the coding process. Coding discrepancies will be resolved through whole group discussion. Youth co-researchers will collaborate with the academic research team in the analysis process. All analytical outputs will be reviewed and ratified by the youth co-researchers and academic research team collectively.

*Data protection*

The deliberative democracy sessions will be recorded, transcribed, and directly identifying information will be removed. Pseudonymized transcripts and notes will be shared among the research team only via the US cloud-based GDPR-compliant qualitative coding software platform.

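### The Arm 1 vs Arm 2 engagement models leave out day-0 baseline survey completion, an early engagement measure already collected; adding it would be a modest efficiency gain, under two conditions

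*Protocol article*

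**What the plan says.** The Engagement paragraph of the Data analysis plan models participation at a given time by logistic regression, "adjusting for various socio-demographic factors (e.g. age, gender, self-reported history of mental health challenges), governance model (self-choice, or specific model presented) and site" (site in the global model only). For total tasks, "the number of tasks completed by a participant will be modelled using Poisson Regression using the same independent variables as previously stated". For the third outcome, "Time to dropout can be analysed using a proportional hazards model with censoring at the study end"; no covariates are named there. The same paragraph plans a secondary look at the governance effect in these analyses.

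On timing, the Data collection section says of the baseline survey: "For ease of administration, these are divided into four sections". It adds that "These baseline questionnaires are administered on study day zero" and that "On the following day, participants begin their first AI-rotation for weeks one to four". Under Study design: engagement, "Participants in the first arm select their AI topic at the beginning of weeks one, five, and nine"; Arm 2 topics are assigned at random for the same three rotations. The two arms are randomised 1:1, independently of governance group.

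**The concern.** Every outcome in the Arm 1 vs Arm 2 comparison measures engagement: still active, tasks done, time of last task. The planned covariates describe who the participant is, which consent model applied and which country they are in. None describes how the participant has behaved so far. The list of socio-demographic factors is introduced by examples, but it is open only within that class.

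The trial collects a behavioural measure at no extra cost. On the planned schedule, the number of baseline sections completed on day 0 is fixed before the arms first differ. The Introduction expects participation in remote studies to fall off quickly, so someone who does not finish the first task is plausibly someone who will not stay. That is an inference; the protocol gives no figure for it.

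What is at stake is efficiency alone. All analyses are also run within site, on a third of the sample, where information is scarcest.

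**Working it through.** **The plan's own figures.** Recruitment: 3 × 1500 = 4500. The goal of 100 completers per country implies 100/1500 = 6.67% completing 12 weeks, about 50 per arm per country. The protocol states no alpha, power or effect size, so there is no power figure to reproduce. For context, with 2250 per arm and an assumed two-sided alpha of 0.05, unadjusted power for 6.67% vs 8.0%, 8.5% and 9.0% is 40%, 64% and 83%.

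**Assumptions (none is in the protocol).** q = share completing baseline; RR = ratio of later participation, baseline completers to non-completers; r = correlation of baseline completion with the outcome.

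**Step 1, task counts.** The ratio of unadjusted to adjusted sampling variance of the arm effect is about 1/(1-r²).
- r = 0.2: 1/0.96 = 1.04
- r = 0.3: 1/0.91 = 1.10
- r = 0.4: 1/0.84 = 1.19
- r = 0.5: 1/0.75 = 1.33

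Simulated Poisson models with robust standard errors (n = 4500, 300 runs, q = 0.6, week-12 retention 12-14%) gave ratios of 1.02, 1.04 and 1.09 at r = 0.10, 0.18 and 0.26. Power rose by only 0.4 to 1.6 points. A further simulation of 150 runs at r = 0.28 gave a ratio of 1.10, with power going from 58% to 67%. That rise is more than the ratio supports. Power of 58% corresponds to a mean test statistic of 1.96 + 0.20 = 2.16; multiplied by √1.10 this is 2.27, or power of about 62%. The variance ratio is the safer summary.

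**Step 2, how much baseline completion can explain at week 12.** With overall participation p, p0 = p/(1-q+q·RR) and p1 = RR·p0, the share of variance explained is q(1-q)(p1-p0)²/[p(1-p)]. For p = 0.0667, q = 0.6, RR = 3: p0 = 0.0303, p1 = 0.0909, and the share is 0.24 × 0.0606²/0.0622 = 1.4%. Over q from 0.3 to 0.95 and RR from 2 to 5 it runs from 0.1% to 5%. If no baseline non-completer finishes, the ceiling is 16.7% at q = 0.3, 4.8% at q = 0.6 and 1.8% at q = 0.8.

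**Step 3, logistic outcomes.** Simulation, N = 4500, 1:1, 1000 runs per row; conditional odds ratio 1.4 at week 12 and 1.2 at the interim time. Entries are unadjusted → adjusted.

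| Outcome | q, RR | Power (%) | Standard error | Log odds ratio |
|---|---|---|---|---|
| Week 12, 6.67% | 0.6, 3 | 84.5 → 84.9 | 0.1122 → 0.1131 | 0.329 → 0.335 |
| Week 12, 6.67% | 0.6, 10 | 83.8 → 85.2 | 0.1125 → 0.1148 | 0.326 → 0.339 |
| Week 12, 6.67% | 0.8, 10 | 84.7 → 85.4 | 0.1123 → 0.1132 | 0.336 → 0.342 |
| Week 12, 6.67% | 0.3, 10 | 78.0 → 81.2 | 0.1129 → 0.1191 | 0.304 → 0.337 |
| Interim, assumed 30% | 0.6, 3 | 73.8 → 77.3 | 0.0641 → 0.0672 | 0.166 → 0.182 |
| Interim, assumed 30% | 0.6, 10 | 62.3 → 71.6 | 0.0642 → 0.0726 | 0.145 → 0.182 |

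The standard error rises in every row. Power rises because the conditional log odds ratio moves further from zero than the standard error grows: in the last row 0.145/0.0642 = 2.26 against 0.182/0.0726 = 2.51.

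Neither the within-site models nor the time-to-dropout model was simulated.

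**The case against.** The strongest reply is that nothing here is wrong. Randomisation protects the arm comparison with or without the covariate, topic choice is a secondary aim of a feasibility study, the modelling language is permissive, and a full analysis plan that is not shown may list more covariates. All of that stands, and it limits the point to an optional improvement.

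Other parts of the reply also stand:
- A reader might infer that the models adjust for socio-demographic factors alone. They do not; governance model and site are in the same sentence.
- A reader might infer that every standard error is larger than it need be. That fails for the logistic models, where adjustment raises it and also changes the target from a marginal to a conditional odds ratio. For counts, the model-based Poisson standard error does not show the gain: in one simulation (r about 0.13) it was 0.0100 both ways, while the true sampling standard deviation went from 0.0579 to 0.0577.
- A reader might expect the most benefit at week 12, where completers are few. The gain is smallest there.
- The protocol does not say when the engagement arm is revealed, whether baseline must be finished before the first rotation, or whether baseline sections count as tasks. If the arm is shown first, the covariate is no longer pre-exposure. If baseline gates entry, the covariate does not vary and gains nothing.

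What the reply does not remove is that, on the planned schedule, a plausibly prognostic measure precedes the exposure and the stated covariates omit it.

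**Conclusion.** The point holds as a minor efficiency suggestion. The documents support three facts: the named covariates include no early engagement measure, the baseline survey yields one, and it is scheduled before the first topic is chosen or assigned. They do not support a claim of bias, of an invalid comparison, or of a known loss of precision.

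The size depends wholly on assumed r, q and RR. For task counts the variance ratio is about 1.02 to 1.09 at r of 0.10 to 0.26, and would reach 1.33 only at r = 0.5. For participation, power rises by roughly 3.5 to 9 points at an assumed 30% interim rate and by 0.4 to 3.2 points at the 6.67% implied for week 12. The benefit requires that the arm is concealed until baseline is over and that baseline completion varies among those analysed.

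**What to change.** First confirm from the app build that the arm is not shown before the baseline survey and that completing it is not a condition of entry. If both hold, pre-specify the number of baseline sections completed on day 0 (0-4) as a covariate in the Arm 1 vs Arm 2 logistic, count and time-to-dropout models. Count outcome tasks from day 1, so that the covariate is not part of the outcome. For the count model, use a robust standard error; otherwise the gain will not appear in the reported interval.

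Leave this covariate out of any model that estimates the governance effect. The baseline survey follows the governance-specific consent, so completion may itself be affected by the governance group.

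The cost is one covariate line, a stated start day for the task count, and a separate model fit for the governance effect. No new data are needed. Pre-specification matters because adding the covariate after the data are seen would look selective.
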